### 175 Sample size calculation

176 Hepatic fat fraction is the primary outcome of this study. However, as there was no  
 177 previous information available in the scientific literature allowing us to perform  
 178 calculations, the required sample size was determined for secondary outcome variables  
 179 intimately associated to hepatic fat accumulation, i.e., visceral adiposity, insulin  
 180 resistance and total body fat. Likewise, we expect that pre-post intervention differences  
 181 in our design consisting in two experimental groups, control and exercise group, will  
 182 have a size effect ( $d$ -cohen) of 0.5 for visceral fat (N=64 in each group, 80% power and  
 183  $\alpha$  of 0.05 and 0.7 for insulin resistance and total body fat percent (N=34 in each group,  
 184 80% power and  $\alpha$  of 0.05). Previous studies have reported losses to follow-up between  
 185 4% and 17%. Assuming a maximum loss of follow-up of 20%, we plan to recruit a total

of 160 overweight children, 80 children for each group. These effect size estimates are based on previous studies performed in overweight children with similar age range and a similar intervention program (22, 29, 30).

## Randomization

Eligible participants will be randomly assigned after completing the baseline measurements to either the control or exercise groups (Figure 1). Randomization of the participants into control or exercise group will be computer generated using IBM-SPSS-Statistical software. Assessment staff will be blinded to participant randomization assignment.

[figure not shown]

**Figure 1.**

## Exercise training intervention

The exercise group will do exercise 3 days/week, 90 minutes per session, over a 22-week period. The program will be offered to the families from Monday to Friday, five days per week to choose a total of 3 days/week. Sessions will be held in the exercise training facilities of the Faculty of Physical Activity and Sport Sciences of the

202 University of the Basque Country (Vitoria-Gasteiz, Spain) and will be supervised by  
203 exercise specialists. The exercise program consists of cardiovascular endurance and  
204 muscle strength exercises. Each session starts with 10 min of warm-up period consisting  
205 of two games of 5 min each and will end with 5 min of cool-down period consisting  
206 mainly of stretching exercises. The main part of the exercise session consists of 60  
207 minutes of moderate to vigorous aerobic exercises. Individual exercise intensity is  
208 calculated from ventilatory thresholds (31) and from the percentage of maximum heart  
209 rate (32) obtained from cardiopulmonary exercise test with respiratory gas analyses in  
210 treadmill ergometer. The training sessions will be developed to progressively increase  
211 the intensity of the aerobic exercises over the 22 weeks. The aerobic workout consists of  
212 games and other simple activities and start-and-stop activities. The emphasis of the  
213 program will be on intensity and enjoyment. More than 80 activities or games have been  
214 selected based on easy of comprehension and fun. These activities include popular  
215 running games and some circuits, and have been categorized according to the physical  
216 activity intensity. The selection of the activities or games according to their  
217 categorization will permit to increase progressively the time on vigorous intensity  
218 exercise over the intervention. Finally, each session concludes with 10 minutes of 6-7  
219 resistance exercises in sets of 10-12 repetitions using therabands, fitballs and/or  
220 autoloads, involving all major muscle groups (quadriceps, hamstring, abductors,  
221 adductors, calves, pectoral, dorsal biceps, triceps and deltoids). Participants will wear a  
222 heart rate monitor (Polar RS300X) during the exercise sessions to ensure achievement  
223 of the target heart rate zone. Heart rate monitors will be programmed according to  
224 individual ventilatory thresholds and % of maximum heart rate.

## 225 Rationale and design of the healthy lifestyle education and psychoeducation 226 interventions

227 *Rationale:* Obesity is associated with many physical and psychological consequences.

228 A family-based, lifestyle intervention with a behavioural program aimed at changing  
229 dietary habits, physical activity levels and sedentary patterns provide significant  
230 decrease of overweight in children as compared to the standard care in the short and in  
231 the long-term (16, 33). Moreover, family-based lifestyle interventions can improve  
232 psychological well-being in overweight and obese children (19, 34). Therefore, the  
233 EFIGRO study will include a family-based healthy lifestyle education program  
234 conducted by experienced nutritionists.

235 Psychological factors are important determinants for behaviour changes in the treatment  
236 of obesity in children (33). Moreover, the concept of eating as a means of coping with  
237 stressors/negative emotions, i.e., emotional eating, is a mechanism by which emotion  
238 regulation relates to obesity (35). Depression, low self-esteem and bullying are much  
239 more frequent in overweight and obese children than in their non-overweight peers (17,  
240 36). Therefore, the intervention will include a family-based psychoeducation program  
241 leaded and conducted by an experienced psychologist in behaviour changes.

242 *Design:* The control and the exercise group will attend both the healthy lifestyle  
243 education and psychological education programs. Sessions will be delivered to both  
244 parents (or caregivers) and children, separately. Being aware that the intervention  
245 program demands time to the families and that this could affect the adherence to the  
246 intervention, the healthy lifestyle education and psychoeducation interventions will be  
247 developed simultaneously. Likewise, families will come to the facilities (rooms) of the  
248 Faculty of Physical Activity and Sport Sciences of the University of the Basque Country  
249 11 times for 90 minutes, once every two weeks, over the intervention. Children will  
250 attend first the healthy lifestyle education program (45 minutes/session), while their  
251 parents or caregivers are participating in the psychoeducation program (45

minutes/session), and after children will participate in the psychoeducation program, while their parents or caregivers are attending the healthy lifestyle education program.

#### *Aims and content of the healthy lifestyle education program*

The family-based healthy lifestyle education program focuses on promoting changes in three lifestyle behaviour areas known as most relevant lifestyle-related risks for obesity and its co-morbidities: diet, physical activity, and stress (37-40). The aim of the program is to increase children's and parents' self-efficacy, knowledge and motivation to adopt healthier dietary habits, increase physical activity level, reduce sedentary behaviour, and reduce stress. To achieve these objectives, the intervention program includes eight sessions combining different aspects of healthy behaviours with the help of teaching materials such as photographs, power point slides, stories, games such as crosswords, riddles, discussions, etc., and three workshops designed by research nutritionists for children and their parents or carers. Key messages will be consistently included across all sessions. The topics included in the program have been selected because of their relationship with hepatic fat deposition or excess adiposity (41-45). Other healthy dietary habits not directly associated with adiposity, but related to cardiovascular disease risk, such as the reduction of the dietary salt content, will be also recommended in the context of a healthy diet, but they do not constitute aims or topics of the program. The content and topics of the sessions are described in **Table 2**.

**Table 2.** Objectives and topics of the healthy lifestyle education program.

|                | Topics and aims                                                                                                                                                                                                                   | Type of session |
|----------------|-----------------------------------------------------------------------------------------------------------------------------------------------------------------------------------------------------------------------------------|-----------------|
| First session  | To learn how to classify foods according to their sugar and fat content                                                                                                                                                           | Lesson          |
| Second session | To promote the consumption of a healthy and complete breakfast understanding its importance for health                                                                                                                            | Lesson          |
| Third session  | To promote the increase in daily physical activity level up to 30 min/day and the reduction of time spent on sedentary behaviours such as TV viewing, computer and video games, and smart phones explaining why this is important | Lesson          |

|                  |                                                                                                                                                                                                  |                                                                                                        |
|------------------|--------------------------------------------------------------------------------------------------------------------------------------------------------------------------------------------------|--------------------------------------------------------------------------------------------------------|
| Fourth session   | a) To learn about the importance of eating five times a day for health and body mass control
b) To learn about healthy options for morning and afternoon snacks                               | Lesson                                                                                                 |
| Fifth session    | To enhance daily consumption of fruits and vegetables                                                                                                                                            | Workshop:
healthy cooking workshop to prepare a common recipe                                       |
| Sixth session    | To reduce the consumption of energy dense foods and sugar sweetened drinks                                                                                                                       | Workshop:
To weigh the sugar content of some foods and beverages typically consumed by the children |
| Seventh session  | To promote the increase in daily physical activity level up to 60 min/day and the reduction of time spent on sedentary behaviours such as TV viewing, computer and video games, and smart phones | Lesson                                                                                                 |
| Eighth session   | To distinguish between hunger and appetite to enhance awareness of the importance of an adequate sleep duration                                                                                  | Lesson                                                                                                 |
| Ninth session    | To learn and understand the nutritional information of food labelling                                                                                                                            | Lesson                                                                                                 |
| Tenth session    | To clarify certain popular myths related to some foods                                                                                                                                           | Lesson                                                                                                 |
| Eleventh session | To practice and integrate the knowledge acquired                                                                                                                                                 | Workshop:
to develop complete and healthy menus                                                     |

272

273 Written information emphasizing key messages will be given to parents or caregivers to  
274 take home after the workshops. To reinforce the messages delivered in the sessions and  
275 workshops and to involve parents or caregivers on lifestyle behaviour changes, there are  
276 matching homework activities planned. Likewise, children will have a booklet with 11  
277 chapters, one chapter per lesson, containing three objectives to follow every day. The  
278 content and fulfilment of the homework activities will be discussed in the next session.

### 279 [Aims and content of the psychoeducation intervention](#)

280 The intervention meetings with parental participation include 11 sessions of 45 minutes  
281 aimed to: (a) increase awareness of the problems that could derive from overweight or  
282 obese children and (b) provide parental skills to get a favourable family environment in  
283 order to make positive changes in their lifestyles and (c) learn assertive communication  
284 skills (46). To achieve these objectives, the intervention program consists of sessions

285 where different topics are presented and discussed, *e.g.*, teasing at school and how to  
286 deal with it, expressing emotions and educating their children in managing them or  
287 changing habits in the family context.

288 The intervention program conducted in the participating children also includes 11  
289 sessions of 45 minutes with the following goals: (a) to ease tools to manage the  
290 emotions and feelings that they experience because of their condition of being  
291 overweight or obese and (b) to provide skills to improve their self-esteem and the  
292 psychological and social well-being. In order to reach these aims, the intervention  
293 program consists of sessions where different topics are presented and discussed, *e.g.*,  
294 teasing at school, putting into words the emotions and feelings that my body makes me  
295 feel or activities such as expressing parts of the body that each one likes of  
296 herself/himself.

#### 297 **Participant retention and addressing compliance and adherence**

298 New activities on a regular basis will be introduced to maintain interest in the exercise  
299 sessions. Children will be invited to suggest appropriate activities. Throughout the  
300 project, the investigation team will be aware that success is primarily dependent on  
301 enjoyment by the children, because the amount and intensity of the exercise rely on the  
302 children's active participation. The staff will continuously try to give the children a  
303 positive experience and will celebrate and reward the success achieving the different  
304 goals of both the healthy lifestyle education and the exercise programs to motivate the  
305 participation and to maintain their interest over the 22 weeks. For instance, working on  
306 the target heart rate range in the exercise program or achieving the goal proposed in the  
307 healthy lifestyle education program (*i.e.*, having healthy breakfast every day, tasting a  
308 different fruit or vegetable every day, etc.) will be rewarded with a smiley emoticon.  
309 The participants will be marked as "absent" if the child does not attend the session or  
310 when he/she refuses to participate on proposed games or exercise activities. Parents will

311 receive telephone calls in case problems pursuing, the child will be dropped from the  
312 program to maintain the integrity and the adherence for the other children. The  
313 attendance of both children and parents or caregivers (as well as who is attending the  
314 session, father, mother, etc.) to the lifestyle education and psychoeducation programs  
315 will be also recorded. Regardless of adherence, participants will be encouraged to return  
316 to post-testing measurements. The adherence to the exercise, healthy lifestyle education  
317 and psychoeducation programs (percentage of attendance) will be used as cofounders in  
318 the statistical analyses.

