## PROTOCOL SUMMARY

Non-alcoholic fatty liver disease is the most frequent liver abnormality observed in overweight or obese children and is strongly associated with metabolic syndrome and insulin resistance. Therefore, the aims of this project are: (i) To evaluate the effect of a 22 weeks multidisciplinary intervention program on hepatic fat fraction in overweight or obese children and (ii) To examine the effect of the intervention on cardiometabolic risk factors, self-esteem and well-being. A total of 160 children, 9-11 years, will be recruited by paediatricians and randomly assigned to control (N=80) or intervention (N=80) groups. The control group will receive a family-based lifestyle and psychoeducation program (2 days/month), while the intervention group will attend the same lifestyle education and psychoeducation program plus the exercise program (3 days/week). The duration of training sessions will be 90min of exercise, including warm-up, moderate to vigorous aerobic activities, and strength exercises. The primary outcome is the change in hepatic fat fraction (magnetic resonance imaging, MRI). Secondary outcomes include cardiometabolic risk factors such as total and adiposity (dual X-ray absorptiometry), visceral adiposity (MRI), functional peak aerobic capacity (cardiopulmonary exercise testing), blood pressure, muscular fitness, speed agility, and fasting blood insulin, glucose, C-reactive protein, alanine aminotransferase, aspartate aminotransferase, gamma glutamyltransferase, lipid profile and psychological measurements (questionnaires). All the measurements will be evaluated at baseline prior to randomization and after the intervention. This study will provide insight in the efficacy of a multidisciplinary intervention program including healthy lifestyle education, psychoeducation and supervised exercise to reduce hepatic fat and cardiometabolic risk in overweight children.

**Trial registration:** NCT02258126

**Keywords:** fatty liver, obesity, children, exercise, metabolic syndrome

61    **LIST OF ABBREVIATIONS**

62    ALT: alanine aminotransferase; AST: aspartate aminotransferase; BMI: body mass  
63    index; CRP: C-reactive protein; Gamma-GT: gamma glutamyltransferase; LDL: low  
64    density lipoprotein cholesterol; NAFLD: non-alcoholic fatty liver disease; TG:  
65    triglycerides; VCO2: carbon dioxide production; VO2max: maximum oxygen  
66    consumption.

67

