## 128 Objectives

129 The primary objective of the EFIGRO study is to investigate the additional effect of  
130 aerobic and strength training on hepatic fat fraction in overweight and obese children  
131 participating in a 22 weeks family-based healthy lifestyle education and  
132 psychoeducation program.

133 Secondary objectives of the study are (i) to examine the additional effect of aerobic and  
134 strength training on cardiometabolic risk in overweight and obese children participating  
135 in a 22 weeks family-based healthy lifestyle education and psychoeducation program  
136 and (ii) to evaluate the additional effect of the exercise intervention in self-esteem and  
137 well-being of overweight and obese children.

138

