#### 514 **Potential confounders**

##### 515 *Pubertal development*

516 Pubertal development will be directly assessed according to Tanner criteria (genital  
517 development and pubic hair) by the paediatricians in the Paediatric Endocrinology Unit  
518 of the HUA.

519 *Physical activity, sedentary behaviour and dietary assessment*

520 Both the control and the exercise groups will attend the same healthy lifestyle education  
521 program. However, differences in changes in physical activity level, sedentary  
522 behaviour and dietary habits could be potential confounders on the effect of the  
523 intervention on hepatic fat and cardiometabolic risk factors.

524 Physical activity will be objectively measured by accelerometry. Children will be asked  
525 to wear an accelerometer on their non-dominant wrist (wActisleep-BT, USA) for seven  
526 consecutive days all the time, except for water-based activities. Thresholds will be used  
527 to classify raw counts per minute into intensities of physical activity (66). Information  
528 about sleep duration and quality will be also obtained from the accelerometers.

529 Participants will also complete a diary log. A self-reported sedentary behaviour  
530 questionnaire (67) will be administered to the children. Participants will report the  
531 frequency of specified sedentary behaviours using predefined response categories  
532 separately for weekdays and weekends. Behaviours to be assessed include watching TV,  
533 playing computer games, playing video games or phone games, surfing the Internet for  
534 recreation, surfing the Internet for study purposes, and studying (nonschool time).

535 Dietary intake will be evaluated by two non-consecutive 24h recalls within a period of  
536 seven days. Children will report all their food and beverage ingestions assisted by  
537 nutritionists. Moreover, dietary habits and patterns will be evaluated by two different  
538 food frequency questionnaires: the KidMed index for the children (68) and a validated  
539 food frequency questionnaire for the parents or caregivers (69). The KidMed index was

540 developed to estimate adherence to the Mediterranean dietary pattern in children and  
541 young adults, based on foods/dietary patterns that sustain it.

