## 566 Data analysis plan

567 The data analysis plan will be defined based mainly in two analyses: i) the per-protocol  
568 analysis, and ii) the intention-to-treat analysis (ITT). For reporting the main findings,  
569 we will use the per-protocol principle which includes children with overweight or  
570 obesity that completed pre and post intervention assessments, and attend at least 50% of  
571 the family-based lifestyle program (no minimum required for exercise program). We  
572 will focus on per-protocol principle because we are interested in knowing the “real”  
573 efficacy rather than effectiveness of our intervention. In addition to the per-protocol  
574 principle, we will also analyse the data using the ITT. Under this principle, we will use  
575 multiple imputation for observations lost at post intervention.

576 The baseline characteristics of the subjects’ in the two intervention groups will be  
577 compared using either the Student t test (for continuous variables) or the  $\chi^2$  test (for  
578 categorical variables). Differences between the intervention groups in terms of  
579 postintervention values for the primary and secondary outcomes will be also examined  
580 using the Student t test. Within group differences (pre vs. post values) in primary and  
581 secondary outcomes will be examined using the Student paired t test  
582 following per protocol and intention-to treat principles. In both the per protocol and the  
583 intention-to-treat analyses, differences between the control and exercise groups in terms  
584 of changes in primary and secondary outcomes will be examined by ANCOVA  
585 adjusting for baseline values. Cohen’s d will be used to estimate the effect size and 95%  
586 CI.

587 Significance will be set at  $P < 0.05$ . All calculations will be made using the Statistical  
588 Package for Social Sciences version 24.0 for Windows (SPSS Inc. Chicago, IL). We  
589 will also use R software (v.3.1.2) for analysis and figures.

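### The protocol conflicts with itself on whether attendance is a covariate; if exercise attendance enters the between-group ANCOVA, the group coefficient no longer measures the added effect of training

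*Protocol*

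**What the plan says.** Four places in the protocol bear on this.

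- **Participant retention and addressing compliance and adherence** (last sentence): "The adherence to the exercise, healthy lifestyle education" "and psychoeducation programs (percentage of attendance) will be used as cofounders in" the statistical analyses. The wording is firm. It names exercise attendance and ties the adjustment to no particular outcome, model or exploratory purpose.
- **Data analysis plan**: in both the per-protocol and the intention-to-treat analysis, group differences in terms "of changes in primary and secondary outcomes will be examined by ANCOVA", "adjusting for baseline values". Attendance is not named as a covariate here. It appears only in the per-protocol definition, which requires at least 50% of the family-based lifestyle programme and sets no minimum for exercise.
- **Objectives**: "The primary objective of the EFIGRO study is to investigate the additional effect of" aerobic and strength training on hepatic fat fraction, on top of the shared education programme.
- **Protocol summary and the design of the education programmes**: "The control and the exercise group will attend both the healthy lifestyle" and psychological education programmes, "while the intervention group will attend the same lifestyle education and psychoeducation program plus the exercise program (3 days/week"). The exercise programme is therefore the only planned difference between the arms.

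A related remark, under Potential confounders, says that differences in changes in physical activity, sedentary "behaviour and dietary habits could be potential confounders on the effect of the" intervention.

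**The concern.** A confounder of a treatment comparison is a common cause of treatment and outcome. Allocation here is random, and attendance is recorded afterwards, so attendance cannot play that role. Exercise attendance goes further: it is the dose of the treatment under test, and no control child can have any.

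The adherence sentence and the Data analysis plan therefore describe two different models for the same comparison. An analyst who follows the Data analysis plan estimates the stated objective. An analyst who follows the adherence sentence estimates something else, with far less precision. Because the protocol does not say which governs, the choice could be made after the data are seen, and a real benefit could be reported as no effect.

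**Working it through.** **1. The plan's own figure.** The Sample size calculation gives d = 0.5 for visceral fat, 64 per group, 80% power and α = 0.05. A two-sided two-sample t-test requires 63.8, so 64 per group, and has 80.1% power at 64. Allowing for 20% loss, 64/(1 − 0.20) = 80 per group, 160 in total. The figures reproduce. The protocol gives no effect size for hepatic fat, so d = 0.5 is borrowed from visceral fat below.

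**2. What the group coefficient means.** Write the model as

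change = b0 + b1·group + b2·(exercise attendance) + b3·baseline,

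with attendance 0 in controls. At a given baseline, an exercise-arm child with attendance a differs from a control by b1 + b2·a. So b1 is the difference at a = 0, and the average effect at mean attendance m is b1 + b2·m. If benefit is proportional to attendance, b1 = 0 and the whole effect sits in b2. If controls were coded missing instead, a complete-case fit would contain no control children. The protocol states neither coding.

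**3. Loss of precision.** With equal arms, attendance of mean m and SD s in the exercise arm, and 0 in controls:

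R² = 0.25m² / (0.25m² + 0.5s²), VIF = 1/(1 − R²), SE multiplier = √VIF.

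For m = 0.75 and s = 0.15: R² = 0.140625/(0.140625 + 0.01125) = 0.926; VIF = 13.5; SE multiplier = 3.67. The unadjusted SE, in SD units, is √(2/64) = 0.177, so the adjusted SE is about 0.65.

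**4. Simulation.** Each scenario used 3,000 or 4,000 simulated trials, 64 per arm, a true effect of 0.5 SD in favour of exercise and residual SD 1. Attendance levels are assumptions; the documents give none.

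| Exercise attendance, mean / SD | SE multiplier (formula) | Benefit proportional to attendance: estimate; rejection rate | Benefit unrelated to attendance: estimate; power |
|---|---|---|---|
| 60% / 25 | 1.97 | about 0; about 5% | 0.50; 28–29% |
| 60% / 20 | 2.35 | about 0; 5% | 0.50; 22% |
| 70% / 15 | 3.45 | about 0; 5% | 0.51; 13% |
| 75% / 15 | 3.67 | about 0; 5% | 0.50; 11% |
| 80% / 15 | 3.90 | about 0; 5% | 0.50; 10% |
| 80% / 10 | 5.74 | about 0; 5–6% | 0.47; 8% |

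With attendance left out and baseline adjusted for, the estimate is 0.49–0.50, the SE 0.18 and power 79–80%. In the proportional case the adjusted estimates lie within about 0.02 of zero.

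**5. Education attendance alone.** When it was simulated as equally distributed in both arms and unrelated to the outcome, adding it left the estimate at about 0.50 and power at 78–80%. The damage above comes from the exercise term.

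**The case against.** The strongest reply is that the only ANCOVA the protocol writes down is sound. The Data analysis plan lists baseline values and nothing else, and run that way it estimates the stated objective at the planned power. The adherence sentence sits in a retention section and names no model. This stands to the extent that a reader who infers that attendance is settled as a covariate in the primary model goes beyond the text. It does not remove the problem, because the Data analysis plan neither withdraws nor limits a sentence that covers the analyses generally.

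Three further inferences are tempting and are not supported.

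- *Adjustment always removes the effect.* This holds only when benefit scales with attendance. If benefit is unrelated to attendance, the estimate is essentially unshifted and what is lost is precision.
- *All three attendance terms do the same harm.* Lifestyle and psychoeducation sessions are open to both arms. Adjusting for them misleads only if allocation affects attendance or if attendance shares causes with the outcome. They are still measured after randomisation and are still not confounders.
- *The protocol also commits to adjusting for mediators.* Under Potential confounders it says only that changes in activity, sedentary behaviour and diet could be confounders. No model containing those changes is stated, and a diet difference might reflect unequal uptake of the shared education as well as a pathway of the exercise. No size can be put on an adjustment that is not planned.

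**Conclusion.** The point holds as an unresolved contradiction, one side of which gives the wrong answer. If exercise attendance enters the between-group model with controls coded 0, the group coefficient does not estimate the additional effect of training. Under the assumed attendance range (mean 60–80%, SD 10–25 points), d = 0.5 and 64 per arm, the analysis then has about 5% power if benefit is proportional to attendance and about 8–29% if it is unrelated, against a planned 80%.

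The exact figures depend on attendance levels that the documents do not give and on an effect size taken from visceral fat. The interpretation of the coefficient depends on neither. The sample size calculation is unaffected.

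**What to change.** 1. In the retention and adherence section, delete the sentence that makes attendance a confounder. Alternatively, limit attendance to descriptive reporting or to an adherence analysis labelled secondary or exploratory, for example a complier-average analysis with randomisation as the instrument.
2. In the Data analysis plan, state that the between-group ANCOVA uses only covariates fixed before randomisation, namely the baseline value of the outcome, and that this model governs.
3. For consistency, add under Potential confounders that post-baseline changes in physical activity, sedentary behaviour and diet are not covariates in that model.

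The cost is a few sentences of wording. No new data, visits or participants are needed.
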